### Interventions

Rehabilitation training will be carried out by technicians who have worked in the burn department for more than two years, and includes massage and passive movement. When to start rehabilitation exercises and the content depend on the patient’s condition. In the early postoperative stage, the skin of patients is relatively tender, and the rehabilitation training that can be given to them is limited. Give priority to passive movement, slightly move the limbs, and try not to touch the newly healed skin, in order to prevent adhesion at the joints. Rehabilitation exercises for patients with good skin healing include active movement and passive movement. When they rely on themselves to move to the maximum angle, the rehabilitation therapist will help them to move to a larger angle, and a lot of pain will occur in this process. Therapists will also massage and release areas where hypertrophic scars are present, with the aim of preventing limited joint movement and scar contracture. Rehabilitation training for burn patients is carried out every day and lasts for a long time. Some patients still need intervention after six to seven years of discharge, which depends on the patient’s condition. The patients included in this study were those who needed daily rehabilitation exercises for a short period of time (within one year) after burn.

The intervention group will be given diluted nitrous oxide inhalation on the basis of conventional treatment. Prior to the intervention, a trained nurse will inform the patient of the use and precautions of the inhalation valve. Two minutes before rehabilitation training, patients in the intervention group will inhale premixed 65% N2O through a mask with a self-controlled inhalation valve until the end of rehabilitation training; The control group will be given continuous oxygen inhalation. These two gases are inhaled and stopped by a patient-controlled valve to facilitate observation of the state of consciousness (the patient will release the valve when the optimal medication status is reached).The intervention will be performed once daily for 30 minutes for 4 weeks.The conventional treatment approach includes the following aspects: 1. The patient uses drugs as directed by the doctor during hospitalization. 2. Therapist’s psychological counseling to patients before and during operation. Patients in both the intervention and control groups will have continuous blood oxygen saturation and heart rate monitored, and blood pressure will be measured before, during and after the intervention. If an adverse reaction occurs, the inhalation should be stopped immediately and oxygen should be given. The adverse reaction will disappear within a few minutes.

### Outcome measures

#### Baseline data.

Demographic data (gender, age, height, weight, country, occupation, etc.) and clinical characteristics (burn site and depth, current pain level, Vancouver scar score) will be recorded for all subjects at T0 (two minutes before intervention). Vital signs, such as blood pressure (BP), heart rate (HR), blood oxygen saturation (SPO2), were also recorded at T0.

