#### Secondary outcome.

The patient’s vital signs, including: oxygen saturation, heart rate, blood pressure, will be measured at T0 (before inhalation), T2 (two minutes after inhalation), and T3 (five minutes after inhalation). At the end of the procedure, the subjects will be asked what side effects occurred during the intervention and the consumption of adjunctive analgesics will be recorded. Patient and technician satisfaction and willingness to re-use analgesic gas were also secondary outcomes. Vancouver scar assessment scale and ADL scale were used to observe the scar improvement and functional rehabilitation of patients at T5(Four weeks after intervention), respectively. The purpose of this study is to control acute pain during burn rehabilitation, and the effect of scar treatment is indirect, so scar score and functional improvement are set as secondary outcomes.

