### Sample size estimation

The degree of pain reduction was the primary outcome of this study. Data for sample size calculations are based on the change in pain levels at T3, as this is the peak of nitrous oxide effect.Percentage changes in VAS scores ≥ 30% were considered clinically meaningful in settings with large differences in basal pain levels. Based on a set of VAS data we previously collected, the effect size at this time was calculated to be 1.68. We employed PASS 17.0 software to calculate the sample size.To assess the effectiveness of this gas analgesic effect, for the bilateral test, we set α (class I error) to 0.05 and test efficacy 1-β to 90% (β = 0.1).After our calculations, using a two-sided, two-sample equal variance t-test, the ability to reject the null hypothesis of zero effect size with a group sample size of 18(9 cases per group) was 91.67% when the overall effect size was 1.68 and the level of significance (alpha) was 0.05.In order to meet the standards of the State Food and Drug Administration and reduce the inadequacy of this study, we decided to recruit a total of 80 patients(40 cases per group).

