### Data management and analysis

In order to ensure the accurate entry of data, two independent personnel enter the data respectively and compare them to ensure consistency. In order to improve quality, researchers are trained before studying. The senior academic statisticians in the group regularly checked the data, including missing values, outliers, etc., and corrected them in time.Missing data from subjects who withdraw from the study will be imputed using multiple imputation methods. Shortly after project initiation, a data monitoring committee (DMC) composition and audit system will be established to monitor data collection and management and patient safety throughout the study. Four professional therapists and nurses, two pain management specialists, and a senior academic statistician who serves as chair of the board will serve as members. Patient safety is monitored and managed by professional therapists and pain management experts.All information will be stored confidentially in the office. Replace all identifying information of the participant, such as name and gender, with a code and always keep it confidential, with only the project manager or attending physician knowing the patient’s personal information. In addition, none of the reports about this study will disclose the personal information of patients.

Statistical analysis will perform using spss.27, with an alpha set at 0.05. The mean (standard deviation), median (interquartile range), minimum value, maximum value and proportion (95% confidence interval) of quantitative data will be listed, and the count data will be described in quantity and percentage. Mean comparison between the two groups will be performed using t-test (normal distribution) and Mann-Whitney test (non-normal distribution). Chi-square test will be used to compare proportions.A value of P < 0.05 will be considered statistically significant.

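### In the readable text the ADL scale has a T5 value but no T0 value, so the secondary outcome of functional improvement cannot be formed unless the schedule figure places ADL at T0

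*Protocol article*

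**What the plan says.** The Protocol article itemises the T0 data under Outcome measures, Baseline data. After the demographic items it says that "clinical characteristics (burn site and depth, current pain level, Vancouver scar score) will be recorded for all subjects at T0", and then "Vital signs, such as blood pressure (BP), heart rate (HR), blood oxygen saturation (SPO2), were also recorded at T0". The ADL scale is in neither list.

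Under Secondary outcome, the Vancouver scale and the "ADL scale were used to observe the scar improvement and functional rehabilitation of patients at T5(Four weeks after intervention), respectively". The closing sentence of that section calls the effect on scars indirect, "so scar score and functional improvement are set as secondary outcomes".

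Under Data management and analysis the stated comparison is unadjusted: "Mean comparison between the two groups will be performed using t-test (normal distribution) and Mann-Whitney test (non-normal distribution").

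**The concern.** Two scales are paired in one sentence and both are described in terms of improvement. One, the Vancouver score, has a stated starting value; the other, ADL, does not. On the readable text, the trial would have a single ADL measurement per patient, taken after treatment.

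From one post-treatment value, neither a change nor a baseline-adjusted difference can be formed. Three things are then lost: precision that costs almost nothing to obtain, the means to see or correct a chance difference in starting function between arms, and the basis for describing the result as improvement. The trial was sized for pain and not for ADL, so precision on this outcome is worth having.

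**Working it through.** **The plan's own figure.** The only power statement concerns the primary pain outcome. There "the effect size at this time was calculated to be 1.68"; "for the bilateral test, we set α (class I error) to 0.05 and test efficacy 1-β to 90% (β = 0.1"); and the power "with a group sample size of 18(9 cases per group) was 91.67"%. For a two-sample equal-variance t-test, df = 2 × 9 − 2 = 16 and the noncentrality is 1.68 × √(9/2) = 3.56. The noncentral t distribution then gives 91.67%, so the figure reproduces. It does not bear on ADL, for which no figure is stated.

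**Where each scale is measured, in the readable text.**

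| Scale | T0 | T5 | Source |
|---|---|---|---|
| Vancouver scar score | yes | yes | Baseline data; Secondary outcome |
| ADL | not named | yes | Secondary outcome |

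No other section gives an ADL baseline. The abstract lists a quality of life score and does not name ADL.

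**What a missing baseline costs.** Inputs: 40 patients per arm (Sample size estimation). The correlation r between T0 and T5 ADL is not given, so r = 0.3, 0.5 and 0.7 are assumed. Results are in units of the ADL standard deviation (SD).

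1. Standard error of a chance baseline difference between arms: √(2/40) = 0.22 SD.
2. Relative to comparing T5 alone, regression on arm and T0 multiplies the variance by 1 − r². The equivalent sample size is 80/(1 − r²).
3. A simple change score multiplies the variance by 2(1 − r).
4. With T5 alone, the difference detectable at 80% power (two-sided 5%) is 0.63 SD. Adjustment multiplies it by √(1 − r²).
5. Power is also shown for an assumed true effect of 0.5 SD. With T5 alone it is 60%.

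| r | 1 − r² | Variance cut | Equivalent n | Detectable difference, adjusted | Power at 0.5 SD, adjusted | 2(1 − r) | Power at 0.5 SD, change score |
|---|---|---|---|---|---|---|---|
| 0.3 | 0.91 | 9% | 80/0.91 = 88 | 0.61 SD | 64% | 1.4 | 46% |
| 0.5 | 0.75 | 25% | 80/0.75 = 107 | 0.55 SD | 72% | 1.0 | 60% |
| 0.7 | 0.51 | 49% | 80/0.51 = 157 | 0.45 SD | 87% | 0.6 | 81% |

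The variance cut in the last row is 1 − 0.51 = 49%, since r² = 0.7² = 0.49; the remaining variance is 51%.

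6. These figures assume that all 80 patients have a T0 value. If only a fraction f has one, and the rest enter with a missing-baseline indicator, the average residual variance is about f(1 − r²) + (1 − f) = 1 − f·r². The reduction shrinks from r² to f·r². Trial status says that recruitment began in April 2025 and was expected to take eight months, so f may be well below 1 for ADL. For the Vancouver score, whose T0 value is already planned for everyone, f should be close to 1.

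**The case against.** The strongest reply is that the deciding evidence is not visible. Fig 1 is the schedule of assessments, with a box for each time point, and it is not shown. It may mark ADL at T0. The section on randomisation also mentions a baseline assessment before the envelope is drawn and does not itemise it. This stands: the point is conditional on the figure. If Fig 1 has ADL at T0, what remains is an incomplete list under Baseline data and an unadjusted analysis.

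Second, the plan defines no ADL change score, and randomised T5 levels can be compared without bias. This also stands. The conflict lies between the word improvement and a single measurement, and rewording would settle that part.

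Third, the gain comes from covariate adjustment and not from calculating improvement as such. This is correct: a change score would be less precise than T5 alone at r = 0.3 and no better at r = 0.5. It is a reason to adjust for T0 instead of subtracting it.

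Fourth, model detail is often left to an analysis plan. That has some force, but the article does state its comparison, and the test it states makes no use of a Vancouver baseline that is already collected.

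A reader might also infer that starting function will vary widely between patients. The documents do not support that. Participants says that patients with similar burn sites and depths will be sought, and Limitation repeats this while admitting that some difference will remain. The point does not depend on it.

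**Conclusion.** The mismatch holds on the readable text: functional improvement is named as an outcome, ADL appears only at T5, and its companion scale has a T0 value. Unless Fig 1 shows otherwise, only T5 ADL levels can be compared.

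A reader might go further and conclude that improvement definitely cannot be calculated, or that the ADL comparison is biased. Neither follows. The schedule figure is unseen, and randomisation protects the T5 comparison. What is lost is precision, the check on chance imbalance (standard error 0.22 SD), and the right to call the result improvement.

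The size depends on an assumed r of 0.3 to 0.7: adjusted variance is 0.91 to 0.51 of the unadjusted, a cut of 9% to 49%, equivalent to 88 to 157 patients instead of 80. For ADL this is an upper bound, because patients already enrolled without a T0 value contribute no gain. The primary outcome and the sample size are untouched.

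**What to change.** 1. Check the schedule figure. If ADL is marked at T0, add it to the list under Baseline data. If it is not, add the ADL scale to the T0 assessments for patients still to be enrolled, completed before allocation. The cost is one short scale at an existing contact and a line on the case report form.
2. Replace the unadjusted tests for these two outcomes by linear regression of the T5 value on arm and the T0 value. For ADL, include a missing-baseline indicator for patients without a T0 value. For the Vancouver score this needs no new data.
3. If a T0 ADL can no longer be collected, rename the outcome as ADL level at T5, compare the levels between arms, and claim no improvement. This costs only a change of wording.

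A T0 value cannot be recovered for patients already enrolled without one, so the benefit for ADL falls with each further patient enrolled before the change.

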#### Primary outcome.

The primary outcome was the the degree of pain reduction in patients. Patients’ pain levels will be assessed using the VAS scale at T0 (before intervention), T2 (two minutes after the start of the intervention) and T3 (five minutes after the start of the intervention). VAS allowed subjects to select a point on a straight line 10 cm long (0: painless, 10: worst possible pain) to report their own pain level [17]. The VAS scale is easy to understand and implement, and it is a widely used pain assessment scale, and it does not interrupt the intervention process of subjects. Gas suction starts at T1 and stops at T4.

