### Participants

All patients with pain caused by rehabilitation training after burn surgery will be invited to participate in this study. In order to reduce complications that may interfere with pain scores during rehabilitation training, we will recruit patients whose burn sites and depths are relatively consistent or close, and the therapists should have more than two years of working experience in the burn department. The inclusion criteria are as follows: men or women at least 18 years old who are willing to participate in the trial and sign the informed consent form; Start functional exercise 3–6 weeks after surgery (with or without skin grafting); Worst pain reported during rehabilitation exercise ≥ 4 (0–10 cm on the visual analog scale (VAS)); There were no postoperative complications. Exclusion criteria included the following: non-primary burn patients; Patients with unconsciousness or abnormal mental status that makes it difficult to report pain scores; Patients with residual wounds or active infections in the scar area; Patients with severe inflammation of the treated area; Patients with contraindications to N_2_O (epilepsy, pneumothorax, lung cancer, chronic obstructive pulmonary disease and acute respiratory infections, abdominal distension or suspected intestinal obstruction, severe inhalation injury, drug-induced or pathological pulmonary fibrosis, maxillofacial injury, diseases involving the ear, nose, throat, e.g., sinuses, otitis media); Drug dependence or abuse; Pregnant or breastfeeding patients.The main inclusion and exclusion criteria are shown in Table 1.

**Table 1 pone.0333378.t001:** Main inclusion and exclusion criteria.

Inclusion criteria	Exclusion criteria
Burn patients with acute pain caused by functional exercise starting 3–6 weeks after surgery	Patients with psychiatric disorders or altered mental status have difficulty reporting pain
Age ≥ 18 years	Patients with non-first burns
Worst pain reported during rehabilitation exercise ≥ 4 (0–10 cm on the visual analog scale (VAS))	Drug dependence or abuse Pregnant or breastfeeding patients

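### The primary VAS ratings stop about 3 minutes into a roughly 30-minute training session and are measured against a pre-training baseline, so they support a conclusion about early-session pain only

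*Protocol article*

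**What the plan says.** All references are to the Protocol article.

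- **Objective (end of Introduction):** efficacy and safety of diluted nitrous oxide for acute pain that rehabilitation training causes.
- **Participants:** eligibility rests on "Worst pain reported during rehabilitation exercise", with a VAS of at least 4.
- **Interventions:** "Two minutes before rehabilitation training, patients in the intervention group will inhale premixed 65% N2O", and inhalation continues until training ends. The intervention lasts 30 minutes, once daily, for 4 weeks. When the therapist takes the limb past the patient's own maximum angle, "a lot of pain will occur in this process".
- **Baseline data:** current pain level is recorded at "T0 (two minutes before intervention").
- **Primary outcome:** the degree of pain reduction, with VAS at T0 and at "T2 (two minutes after the start of the intervention) and T3 (five minutes after the start of the intervention"). T1 is when the gas starts and T4 when it stops. Neither is listed as a VAS time.
- **Secondary outcome:** vital signs use the same labels, counted from the gas: "T0 (before inhalation), T2 (two minutes after inhalation), and T3 (five minutes after inhalation").
- **Sample size estimation:** based on the change in pain at T3, described as the peak of the gas effect. A percentage change in VAS of at least 30% is called clinically meaningful.
- **Discussion:** puts the peak effect at two minutes.
- **Abstract, Method:** labels the times differently and gives five minutes after the start twice, once as T2 and once as T3.

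**The concern.** The trial asks about pain during training and selects patients on their worst pain during training. Its primary ratings, however, are tied to the start of the gas. Read with the two-minute lead-in, they lie before training, at its start and shortly afterwards. Three things follow.

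- Most of the session contributes nothing to the primary outcome. A benefit that fades, or one that appears only later, would not be seen.
- The baseline is taken before the painful stimulus. A change from that baseline is not a reduction of training pain: pain may rise in both groups while the gas is working.
- The stated reason for choosing T3 is the timing of the drug effect, not of the training pain, and the article gives two different times for that peak.

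At stake is the scope of the claim. A positive or negative result at T3 could be reported as applying to rehabilitation sessions as a whole, when it describes only their opening minutes.

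**Working it through.** **Step 1: place the ratings on the training clock.** Inputs: gas starts 2 minutes before training (Interventions), T2 and T3 are 2 and 5 minutes after the start (Primary outcome), T0 is 2 minutes before the start (Baseline data), and the session lasts 30 minutes (Interventions).

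With the clock starting at the gas, minutes into training = minutes since gas start − 2.

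| Rating | Clock starts with gas | Clock starts with training |
|---|---|---|
| T0 | −2 − 2 = −4 | −2 |
| T2 | 2 − 2 = 0 | 2 |
| T3 | 5 − 2 = 3 | 5 |

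The first column is the better supported. Secondary outcome counts the same labels from inhalation. In the second column T0 would coincide with gas start, which has its own label, T1.

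**Step 2: share of training left unrated after T3.**

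- Gas clock, 30 minutes counted from gas start: training is 30 − 2 = 28 minutes; 3/28 = 10.7% elapsed, about 89% unrated.
- Gas clock, training itself 30 minutes: 3/30 = 10%, so 90% unrated.
- Training clock, 30 minutes: 5/30 = 16.7%, about 83% unrated.

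**Step 3: what a change from T0 measures.** The article gives no VAS distribution, so these values are assumptions for illustration. Suppose VAS at T3 is 6 on oxygen and 4 on nitrous oxide, a true difference in training pain of 2 cm, or 2/6 = 33%. Change from T0 is then:

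| Assumed T0 | Oxygen, cm (%) | Nitrous oxide, cm (%) | Difference, cm |
|---|---|---|---|
| 1 | +5 (+500%) | +3 (+300%) | 2 |
| 2 | +4 (+200%) | +2 (+100%) | 2 |
| 4 | +2 (+50%) | 0 (0%) | 2 |
| 6 | 0 (0%) | −2 (−33%) | 2 |

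The between-group difference in centimetres is 2 throughout. The percentage change depends mostly on T0. In this example a 30% reduction from T0 is reached only when pain before training already equals the control group's training pain. At T0 = 0 the percentage is undefined.

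**Step 4: does the sample size stand in the way of a later rating?** The plan's own figure reproduces. For a two-sided t-test with n per group, degrees of freedom are 2n − 2 and noncentrality is d√(n/2). With n = 9, d = 1.68 and alpha 0.05, power is 91.67%, as stated. With the planned 40 per group, power is above 99.9% at d = 1.68, 90% at d = 0.73 and 80% at d = 0.63. A later rating could show a much smaller standardised effect than 1.68 and still be tested adequately.

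**The case against.** The strongest defence is that T3 does lie inside training, that it was chosen to rate pain under an established gas effect, and that randomisation protects the comparison at that time. A rise in pain common to both groups cancels when means are compared, as the constant 2 cm above shows. This stands: the T3 comparison is valid for early training.

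The clock can also be disputed. Primary outcome does not define the start of the intervention, the schedule figure is not available here, and the repeated five-minute point in the Abstract may be a slip for a later rating. This also stands, and it is why reconciling the time points comes first. It does not remove the point: the alternative clock still leaves about 83% of training unrated, and the Primary outcome text lists no later VAS.

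A reader might be tempted to go further in three ways that the article does not support.

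- **That patients with severe pain late in the session would be classed as successes.** No responder endpoint is defined. The 30% figure is a relevance benchmark, and the planned tests compare group means.
- **That percentage reductions would be negative or undefined in many patients.** No T0 distribution is given, so the frequency is unknown.
- **That the unrated minutes are those in which the therapist moves the limb past the patient's own range.** Interventions gives an order of events, not a time, and does not exclude the first three minutes.

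Finally, replacing the primary outcome has a price. Trial status reports that recruitment began on April 7, 2025, the effect size of 1.68 was derived for T3, and a worst-pain score at T4 is recalled just after a sedating gas. These are reasons to prefer adding a rating to replacing the primary outcome.

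**Conclusion.** The point holds in a limited form and should be fixed. As written, the primary outcome supports a conclusion about pain in roughly the first 3 minutes of training (5 on the alternative clock), with 83% to 90% of training unrated, while the objective concerns pain caused by training in general. The T0-to-T3 change, and the 30% benchmark applied to it, do not measure reduction of training pain because T0 precedes training. The comparison between groups at T3 is sound for what it covers, and power is not the problem.

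This rests on the Primary outcome section giving the complete list of VAS times and on a training length of 28 to 30 minutes. Whether pain late in the session differs from pain at T3, and in which direction, cannot be known from the article.

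**What to change.** 1. **Reconcile the time points** in the Abstract, Interventions, Primary outcome, Secondary outcome, Sample size estimation and Discussion: one clock origin, one set of labels, and one statement of when the gas effect peaks.
2. **Add two ratings:** one VAS at a fixed mid-session time, and one at T4 for worst pain during the session. Make them a key secondary outcome. They should become primary only by a dated amendment made before unblinding that covers patients already enrolled, names the session or sessions that count among the daily sessions over 4 weeks (4 × 7 = 28), and notes that 1.68 was derived for T3.
3. **Change the comparison:** analyse VAS during training between groups, adjusted for the worst exercise pain recorded at eligibility and for T0, in place of percentage change from T0.
4. **If T3 remains primary,** limit the stated conclusion to early-session pain.

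The cost is one or two extra VAS marks per session. Primary outcome itself says that the scale does not interrupt the intervention. Some recall error under sedation at T4 is likely, and the mid-session rating partly covers it. Changing the primary would also require updating the registry entry.
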